**Fig. 2 Fig2:**
[figure not shown]
Study design. CIMT, Constraint-Induced Movement Therapy; mos, months; tDCS, Transcranial Direct Current Stimulation

##### Rationale for use of tDCS

Our previous research incorporated rTMS, which although promising as an intervention, has limitations especially with children [36, 37]. Our recent results demonstrate not only safety and but also reveal significant improvements in hand function with rTMS combined with constraint-induced movement therapy, yet we foresee the possible greater benefits from using tDCS over this type of non-invasive brain stimulation in pediatric hemiparesis. (REF) First, both of the interventions, tDCS and CIMT, applications of tDCS/CIMT can occur concurrently whereas it is difficult to incorporate the use of rTMS *at the same time* as performing behavioral therapy with the affected upper extremity. Applying tDCS/CIMT simultaneously could optimize neuroplastic principles of concurrent firing of neurons and strengthening of neuronal networks [38, 39]. Second, tDCS may reduce costs. As rTMS can be ten times the current cost of tDCS, cost may become prohibitive when considering rTMS. Additionally, if the application of tDCS reduces the need for additional therapies, a further costs savings could be realized. Third, use of rTMS has resulted in reports, albeit rare, of adverse events such as seizures and syncopal episodes, in both adults and children [40, 41] .

In addition to its economy and portability, tDCS has shown improvements in motor function in adults with and without the concurrent use of CIMT [42, 43]. The rationale for the investigation of tDCS in the pediatric population is that the use of non-invasive brain stimulation could translate more efficiently into clinical applications thus improving the quality of life for children with hemiparesis. And tDCS safety, when using standard guidelines, is supported in the literature as to having common side effects limited to mild and reversible skin irritation. Specific to the tDCS model we are using (Soterix LTE 1×1 tDCS, NY, NY), the design reduces skin irritation by conditioning the skin prior to stimulation and allowing the device operator to incorporate subject feedback and adjust the controls without stopping. This model was specifically chosen for our project because of its adaptability to resistance changes between the surface electrodes and the subject. The model uses two 9 V batteries to administer stimulation. As a safety feature, the unit will automatically reduce the applied voltage so as to maintain a low voltage level. The built-in ramp-up and ramp-down features allow for gradual administration of the current. Another component of this device specifically designed for children is the adjustable strap that allows for optimal contact of the surface electrodes with the skin for reduced irritation.

Safety. Safety testing includes a physician screening with a modified pediatric stroke outcome measure at pretest, interim day 5, posttest and follow-up sessions. Additionally, vital signs are assessed before and after each tDCS/CIMT session and subjects and caregivers complete a subject report of symptoms and a tolerance survey.

Corticospinal tract integrity using MRI Sequences. Resting state fMRI (rs-fMRI) and Diffusion Tensor Imaging (DTI) techniques are becoming alternatives to more traditional task fMRI and structural MRI scans to demonstrate functional and structural connectivity in the brain, particularly in pediatric patients who may be challenged by participating in task based fMRI studies. Our previous work revealed cortical volume differences in children with hemiparesis; further investigation using connectivity metrics may provide a better understanding of the integrity of the corticospinal tract in congenital hemiparesis. Subjects will be scanned at UMN Center for Magnetic Resonance Research on a Siemens 3 T system to obtain a) T1-weighted structural MPRAGE with a 1 mm isotropic spatial resolution; b) High angular resolution multi-band diffusion imaging (HARDI) with whole-brain coverage, 90 slices with 1.5 mm isotropic spatial resolution, b-values of,1000 and 2000 s/mm^2^ with 64 gradient directions per b value, and 16 additional non-diffusion weighted images and c) Resting-state multi-band based functional MRI will be obtained with whole brain coverage, 72 slices with 2 mm isotropic slices, TR = 730 ms, and 500 time points in 6 min. The complete dataset will be obtained in less than 45 min, taking into account time required for setup and comfortable installation of the child in the scanner. Resting-state fMRI data will be processed using independent component analysis (ICA) to identify the sensory-motor area. Activation areas on the baseline scans will be used to refine the site of tDCS and identify seed areas for tractography.

Excitability Measurements using TMS*.* TMS (Magstim, Dyfed, UK) will be used to measure corticospinal excitability in the ipsilesional and contralesional hemispheres. TMS will be delivered with a 70-mm figure-of-eight coil, tangential to head with handle aligned 45 degrees lateral. The assessment will incorporate single-pulse motor threshold, 1 mV and cortical silent period testing. TMS measurements of cortical excitability guided by stereotactic neuronavigation (Brainsight, Rogue Research, Montreal, QC, Canada), will be employed to create a map of the motor cortex from anatomical MRI images obtained at the CMRR. The co-registration of the TMS coil position on the head with the MRI obtained image of the brain anatomy will allow precision in children who have neurologic lesions. All TMS testing will occur in the UMN CTSI by the PI. For this, the child will be seated in a child-sized reclining chair. Surface electromyographic (EMG) electrodes will be attached over the first dorsal interosseous muscles bilaterally, which will record the motor evoked potentials (MEP) resulting from the magnetic stimulation to the M1 region of each hemisphere. Next, the resting motor threshold (RMT) for TMS activation of the target muscle will be determined, and the location of the hotspot defined. If a threshold cannot be elicited within at least the contralesional hemisphere (i.e., no hotspot), the subject will be excluded from the study as position of the tDCS electrodes will be influenced. The RMT will be defined as the lowest amount of stimulation inducing an MEP of at least 50uV on at least 3 of 5 stimulations Cortical excitability will also be tested by administration of 10 TMS pulses, at the minimum stimulus intensity to produce MEPs of 1 mV [44].

CSP will be determined by the subject exerting finger extensor contraction at approximately 30 % of maximum, as guided by a force tracing on a computer display, while a single TMS pulse at an intensity of 150 % of RMT is delivered to the ipsilesional M1 cortex [45, 46]. The resultant CSP will be measured from the onset of the first peak of the MEP to resumption of surface EMG activity with a threshold value of 50 % mean prestimulus amplitude [47].

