**Methods/design:**

A randomized, controlled, double-blinded clinical trial. Twenty children and/or young adults (ages 8–21) with congenital hemiparesis, will be enrolled. The intervention group will receive ten 2-hour sessions of transcranial direct current stimulation combined with constraint-induced movement therapy and the control group will receive sham stimulation with CIMT. The primary outcome measure is safety assessment of transcranial direct current stimulation by physician evaluation, vital sign monitoring and symptom reports. Additionally, hand function will be evaluated using the Assisting Hand Assessment, grip strength and assessment of goals using the Canadian Occupational Performance Measure. Neuroimaging will confirm diagnoses, corticospinal tract integrity and cortical activation. Motor cortical excitability will also be examined using transcranial magnetic stimulation techniques.

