### Hypotheses

Children with hemiparesis randomized to intervention (tDCS/CIMT) or control (sham tDCS/CIMT) will not display any seizure activity or other serious adverse effect.The intervention group will show greater improvement in paretic hand function (force production, speed, quality of movement) than will controls.The intervention group will show greater improvements in self-reported levels of participation and satisfaction with rehabilitation goals as evidenced by the COPM.

The secondary objective is to examine the influence of combined tDCS/CIMT on brain excitability and reorganization.

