### Blinding

The investigator who performs the testing, the CIMT interventionists and the physician who does the evaluations will be blinded to the treatment arm as will the child/caregiver/family. The study biostatistician, study coordinator and principal investigator (PI) will be unblinded. The following procedure will be employed:The study biostatistician will provide sealed envelopes to the study coordinator.The study coordinator will share the group assignment with the principal investigator in a secure private room, in the absence of the physician, research tester, subject legal guardian and subject. The Medical Monitor to the study will have access to the group assignment.Blinding is applied through designated settings on the tDCS machine of sham or real tDCS. The unblinded investigator who administers the tDCS (PI: [name]) will, during the intervention, switch the setting on the tDCS device to the designated placebo setting, hidden from view of the subject. For the first 30-seconds of either setting, a gradual “ramp-up” sensation of the stimulation occurs. This is built into the machine for both settings. However, for the sham stimulation, the sensation then abates, and not until the end of the 20-minute session does the subject receiving the 30-seconds of “ramp-down” sham once again experience the sensation. The sensation then occurs and “ramps-down” the amperage until the machine turns off.Information on subject group assignment will be logged and stored in a designated locked cabinet at the study coordinators office.

Outcome Assessments. We incorporated the body function/structure and activity/participation domains of the International Classification of Functioning, Disability and Health [2727].

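### TMS excitability outcomes are measured by the unblinded principal investigator, so they are not assessor-blinded as the Blinding section implies

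*Protocol article*

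**What the plan says.** The Methods/design part of the abstract labels the trial "A randomized, controlled, double-blinded clinical trial".

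The Blinding section divides the staff into two groups:

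- Blinded: "The investigator who performs the testing, the CIMT interventionists and the physician who does the evaluations will be blinded to the treatment arm".
- Unblinded: "The study biostatistician, study coordinator and principal investigator (PI) will be unblinded".

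It describes how the PI learns the arm: "The study coordinator will share the group assignment with the principal investigator in a secure private room, in the absence of the physician, research tester". It also identifies the PI as the person who delivers the stimulation: "The unblinded investigator who administers the tDCS (PI".

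The paragraph on excitability measurements using TMS (under Rationale for use of tDCS) assigns the measurement: "All TMS testing will occur in the UMN CTSI by the PI".

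TMS is the article's measure of corticospinal excitability. The second objective depends on it in part: "The secondary objective is to examine the influence of combined tDCS/CIMT on brain excitability and reorganization". Under that objective, the article predicts greater ipsilesional excitability with active stimulation than with sham, and a correlation between brain changes and motor gains. The statistical analysis paragraph examines the second prediction by linear regression and sets significance at p < 0.05.

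**The concern.** One section promises a blinded tester. Another gives a whole class of outcome tests to the person who has been told the allocation and has delivered active or sham current over ten sessions. Both statements cannot hold for TMS.

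The secondary hypothesis is directional and between-group. If the operator knows the arm, small unintended differences in how the measurement is made could favour one arm and look like a treatment effect on excitability. The same measurements feed the regression on motor function, so a distortion there would carry into the mechanistic conclusion. Choices made live, such as where the coil sits and which intensity is accepted, cannot be undone at analysis.

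**Working it through.** The document gives no figure for this point, so the check is a comparison of sections.

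**1. Is the PI blinded?** No. The Blinding section says so directly, describes the disclosure of the assignment, and has the PI operate the device.

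**2. Are the PI and the blinded tester different people?** Yes. The PI is told the arm while the research tester is absent.

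**3. Who does TMS?** The PI. The sentence covers all TMS testing, with no exception for visits after treatment.

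**4. Is there a safeguard elsewhere?** None is described: no second operator, no coded traces, no blinded reading.

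**5. Which measurements are exposed?** Those taken after the PI knows the arm. The eligibility criteria require a motor evoked potential (MEP), so baseline TMS plausibly comes before allocation and would then be unaffected. The visit schedule is in figures that are not shown. However, an analysis of change in excitability needs at least one post-treatment measurement. That covers both groups of 10, so 20 children.

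**6. How much room does the TMS paragraph leave the operator?**

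| Step | Fixed in the text | Left to the operator |
|---|---|---|
| Hotspot and coil | MRI-guided neuronavigation, coil type and angle | choice of hotspot, holding of the coil |
| RMT | at least 50 µV on at least 3 of 5 pulses | how intensity is stepped up or down |
| 1 mV test | 10 pulses, 1 mV target | search for the intensity |
| CSP | 150% of RMT, contraction about 30% of maximum with a force display, end defined at half of mean pre-stimulus EMG | reading of the trace |

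Two links matter for the remedy.

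- The CSP pulse is 1.5 × RMT. An RMT recorded d units of intensity too high or too low therefore moves the CSP pulse by 1.5 × d.
- The article does not say whether the 1 mV intensity is found again after treatment. If it is, part of the result is the intensity chosen live. If the baseline intensity is reused, the result is MEP amplitude, which can be scored offline.

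**7. What is outside the problem?** The text does not have the PI score the AHA, the COPM or grip strength, or carry out the physician's evaluation. It does not assign the resting-state fMRI or diffusion imaging to the PI. The power calculation concerns the AHA, and who performs TMS does not enter it.

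**The case against.** The strongest defence is that the testing in the Blinding section means only the research tester's hand-function assessments. The article would then openly disclose an unblinded PI and contain no contradiction, only a weak design choice for a mechanistic outcome. This reading is possible, but the section makes no exception for TMS. Even if it is accepted, the excitability outcomes are still gathered by someone who knows the arm, under a double-blind label.

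A second defence is that the TMS procedure is tightly specified. This stands in part. The threshold, the CSP end point, the contraction level and the navigation are fixed, so it would be wrong to say that every TMS measure is a matter of judgement. Operator influence is narrowed to the last column of the table above.

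A reader might infer three stronger conclusions that the document does not support:

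- *That the trial's main results are compromised.* A blinded tester and a blinded physician are named for the other evaluations, and the MRI part of the secondary objective is not given to the PI.
- *That the bias can be put at some fraction of a standard deviation.* The article gives no basis for such a figure. Any value would be an assumption, and only a shift that differs between arms would matter.
- *That the CIMT interventionist can see the device setting.* The article has the investigator "switch the setting on the tDCS device to the designated placebo setting, hidden from view of the subject". It does not say the switch is hidden from the subject alone, and it states that interventionists are blinded. How the switch is screened from others is detail that a condensed article can leave out.

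**Conclusion.** The concern holds for the post-randomisation TMS outcomes: RMT, MEPs at the 1 mV intensity, and CSP. As written they are not assessor-blinded, and the Blinding section and the TMS paragraph need to be reconciled. The consequence is confined to the secondary excitability hypothesis and to the excitability part of the regression. It affects all 20 children, but the direction and size of any bias cannot be estimated from the document.

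This is a moderate point about a secondary objective. It rests on two assumptions: that at least one TMS session follows disclosure of the arm to the PI, which the analysis of change implies, and that the full protocol contains no blinded reading that the article omits. If such a reading exists, what remains is the wording and the measurements set live.

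**What to change.** Settle the following before post-treatment TMS data are collected:

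1. **Code and score offline.** Store post-randomisation EMG under IDs that reveal neither arm nor visit. Have the blinded tester already planned score MEP amplitude and CSP from the stored traces, using the article's own thresholds.
2. **Constrain what is set live.** Prespecify a stepping rule for RMT and for the 1 mV intensity, applied at the stored baseline hotspot under neuronavigation. State whether the 1 mV intensity is found again after treatment.
3. **Use a blinded operator only if one is available.** The article does not show that the blinded tester can perform navigated TMS, so reassigning post-treatment TMS depends on an existing blinded staff member being trained for it.
4. **Correct the blinding statement.** If the PI continues to do the testing, say in the Blinding section that TMS acquisition is not operator-blinded, and do not apply the double-blind label to those outcomes.

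The cost is a small amount of data coding and scoring, plus brief training of the scorer if needed. Treatment, sample size and the primary analysis do not change. One limitation remains: with the PI at the coil, RMT setting is constrained by rule but not blinded.

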#### Intervention

##### tDCS/CIMT intervention group

Children randomly assigned to this group will receive 10 sessions of both tDCS and CIMT on concurrent days over a span of two weeks. As supported by results from our previous computerized modeling pilot, the subject will receive tDCS at the motor hotspot at 0.7 mA current intensity for 20 min [19]. In a primary motor cortex (M1)/supraorbital (SO) montage, the anode will be positioned over the ipsilesional supraorbital region and the cathode positioned over contralesional motor hotspot to induce contralesional cortical inhibition. During this 20 min session, the subject will be involved in CIMT for the paretic hand and arm using a sling. The sling will be applied for a 2-hour period, which incorporates the 20 min tDCS session. The CIMT will be given to the subject on an individual basis for two hours each CIMT treatment day by a CIMT-trained therapist/interventionist. The CIMT treatments will be standardized, consisting of shaping activities for function, range of motion and strengthening of the paretic upper extremity. In addition, children will continue to use their paretic limb during functional activities at home and during a caregiver-supervised home program. This combined treatment of tDCS and CIMT will continue until 10 weekday sessions are completed over the two-week period.

##### tDCS/CIMT control group

Children in this group will receive the same procedures and home program as the intervention tDCS/CIMT group but, the tDCS device will be set to a specific placebo setting which extinguishes the current after a 30 s to 1 min ramp-up phase and gradually reintroduces the ramp-down at the end of the 20 min session. This feature allows for placebo control and blinding.

Statistical Analysis. There are 3 analysis populations planned. Intent-to-treat (ITT) will include any subject randomized according to their treatment assignment. Per-protocol (PP) will include randomized subjects without major protocol violations and who were compliant (at least 80 % of planned sessions with their treatment assignment. A detailed list of the major protocol violations warranting exclusion from the PP analysis will be determined prior to trial commencement. The Safety population will include all subjects who receive treatment, according to treatment received. We do not anticipate these groups to differ. The safety profile will use the safety population and be primarily descriptive in nature reporting the number and percentage of adverse events for the two treatment groups and include an aggregate breakdown by severity, seriousness, and frequency (within a patient). Within-group analysis of continuous outcomes comparing posttest to pretest will be done with paired t-tests. Between-group analysis of continuous outcomes comparing the mean change from pretest to posttest between treatment groups will be adjusted for baseline values in the fashion of ANCOVA for added precision. The primary analysis will be based on the ITT population with complementary analyses using the PP population. The association between changes in brain excitability/reorganization and motor function will also be evaluated and based on linear regression. P-values less than 0.05 will be considered statistically significant.

## Discussion

We outline the background and design of a trial with two intervention groups comparing the effects of tDCS on children and young adults with hemiparesis receiving CIMT. The design of this study is predicated upon positive outcomes previously established with CIMT. Additionally, we incorporate consideration of trials we have completed with neuromodulation interventions of repetitive transcranial magnetic stimulation and a tDCS pilot with this population [19, 36, 48]. The proposed study design pursues investigation of a synergistic effect achieved by combining rehabilitation (CIMT) and neuromodulatory (tDCS) interventions. The study hypotheses reflect the importance of safety, feasibility and efficacy surrounding this dual intervention. As non-invasive brain stimulation in pediatric hemiparesis is in a nascent investigational phase, understanding the potential value of such interventions is paramount.

## Abbreviations

AHA: Assisting-Hand Assessment
CP: Cerebral Palsy
CIMT: Constraint-Induced Movement Therapy
COPM: Canadian Occupational Performance Measure
MRI: Magnetic Resonance Imaging
NIBS: Non-Invasive Brain Stimulation
rTMS: Repetitive Transcranial Magnetic Stimulation
tDCS: Transcranial Direct Current Stimulation
TMS: Transcranial Magnetic Stimulation
